## Abbreviations and acronyms

|             |                                             |
|-------------|---------------------------------------------|
| AE          | Adverse event                               |
| ARV therapy | Antiretroviral therapy                      |
| DSN         | Distal sensory neuropathy                   |
| DSMB        | Data & safety monitoring board              |
| EMA         | European Medicines Agency                   |
| EML         | Essential Medicines list                    |
| HIV         | Human immune deficiency virus               |
| MCC         | Medicines Control Council of South Africa   |
| RCT         | Randomised controlled trials                |
| SA NDOH     | South African National Department of Health |
| SAE         | Serious Adverse Event                       |
| SOP         | Standard operating procedure                |
| WHO         | World Health Organisation                   |
| Wits        | University of the Witwatersrand             |

## Trial abstract

A double blind randomised controlled trial to assess the effectiveness of amitriptyline compared to placebo in the management of moderate to severe HIV- related peripheral neuropathy. A cross over design will be used and 124 adult male and female volunteer participants with moderate to severe HIV related neuropathic pain will be followed up for a total of 15 weeks. Sixty two participants will be clinically and virologically stable on ARV drugs and 62 will not be in ARV therapy or intending to start in the next four months. In the first six weeks participants will be given either amitriptyline or identical looking placebo titrated to either effect or a maximum dose of 150mg. Then following a three week 'washout' period, participants will be 'crossed-over' to the other arm and titrated to either effect or a maximum dose for 6 weeks. Pain intensity will be measured on a daily basis and recorded into a pain diary by the participant and regular telephonic contact will be maintained between the study nurse and the participants. Pain intensity using tools validated for neuropathic pain, as well as other data will be collected at face to face interviews at each of the 5 scheduled follow up visit. Data collected will include information on adverse events, physical functioning and quality of life.

## Study Summary

**Study purpose:** to assess the effectiveness of Amitriptyline compared to placebo in the management of moderate to severe HIV- related peripheral neuropathy in a population using ARV and not using ARV therapy

**Study design:** A double blind randomised controlled trial using a cross over design

**Sample Size:** 124 participants; 62 on ARV therapy and 62 not on ARV therapy followed up for a total of 15 weeks

**Study population:** adult men and women with documented HIV infection and moderate to severe HIV related distal sensory neuropathy

Visit schedule: An information session with recruitment, followed by a screening visit and an enrolment visit. After enrolment there will be five scheduled visits and weekly telephonic follow-up if written consent provided for that. Optional visits to the Palliative care centres may be done at any time during office hours for concerns, advice or further information. After hours telephonic contact will be available.

Study duration: the total duration of the study is 14 months. Three months for start up, training and preparation, enrolment closes after 6 months; the last participant exiting at month 11, and three months analysis and write up.

Primary objective: A measurement of the difference in pain intensity at the beginning and end of each 6 week treatment period.

Secondary objective: These will be adverse side effects of treatment, minimum effective doses, maximal tolerated doses, mood and effect on activities of daily living.

Study sites: Participants will be recruited from the Nthabiseng HIV Clinic at the Chris Hani Baragwanath Hospital, the Helen Joseph Hospital HIV clinic, and the palliative care clinic and outreach services.

Regulatory and monitoring: The Medicines Control Council (MCC) approval is not required since the drug is being used for indicated purposes. The MCC will be notified. The trial will be registered with the SA National Trials Register, and the Cochrane trials register. Ethical approval will be sought from the Wits REC and regular progress reports submitted as well as SAE, AEs and protocol violations. A study DSMB will be constituted who will perform an interim analysis as well as monitor the trial for safety and protocol violations.

Ethical issues: Placebo is justified on the basis that there is no comparator established nationally or internationally as yet. A clinician's advice will be sought for those identified with severe DSN pain which may be ARV related and in whose interest a change in ARV regime may be warranted instead of pain relief. Patients *in extremis* in pain will not be eligible and provision for rescue treatment for all participants will be available.

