### ***Cross over design***

A cross over design is proposed for the following reasons: HIV has a complex disease course, and it is acknowledged that there may be many different mechanisms for the DSN so it is desirable if the participant acts as their own control. It is considered that the disease course will not significantly deteriorate in the follow up period of 15 weeks, although the baseline pain intensity will be measured at the start of each treatment intervention. It is anticipated that the follow up period is not too long to see a significant attrition rate. There will be two sub-groups: those stable on ARV with DSN and those not on ARV drugs. Secondly, the disease process is fairly stable over the proposed 14 weeks and the survival times for most participants will be more than proposed trial period.

Washout period: The SAMF 8 cites a plasma  $t_{1/2}$  of 10-50 hours, but also notes that the nortriptyline metabolite is active. The rule of thumb would be 5 half-lives, but in this case, you'd need to track down the metabolite's elimination. (Handbook of Basic Pharmacokinetics including Clinical Applications (6th edition). Ritschel WA and Kearns GL. APHA, Washington, 2004) gives a  $t_{1/2}$  for nortriptyline of 14-90 hours. On that basis, you'd be looking at a wash-out of at least 450 hours, or 18.75 days. Personal correspondence [name]

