## **Primary outcome measures**

Self reported pain intensity measurement is the primary outcome measure.

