## **METHODS**

### **Sample size calculations**

These have been calculated by a statistician, in the Wits School of Public Health.

The sample size will be determined with the following variables considered:

90% power,  $\alpha=0.05$ , effect is difference of 2 on a 0-10 scale; variance is 2SD. Variability of the distribution of the population was estimated from existing local clinical data and from previous estimates in the literature. The size of the placebo effect was estimated after considering the literature. For a cross-over design 46 participants will be required. Assuming two distinct sub-populations, those stable on ARV therapy and those not on ARV therapy and a loss to follow-up of ~10%.

**Enrolment target is 124 participants:** 62 on ARV therapy and 62 not on ARV therapy

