### ***Data collection, management and analysis***

All patients will be allocated a unique identifier that will also serve as their file number on site. All the information for the patient, laboratory results, and questionnaires from different visits, together with the signed informed consent will be kept in the patient's file. The files will be locked up in a cupboard with limited access control.

Double entry of data collected will be entered using Microsoft Access. R statistical package will be used to analyse the data. Descriptive statistics will be used to describe the demographics and clinical characteristics of the population studied.

The primary outcome (pain relief between baseline and end of the study) will be compared for the

- significance of overall pain relief for repeated measures using univariate analysis of variance (ANOVA)
- Association of the drug and the level of pain relief between different subjects using ANOVA.

The number needed to treat (NNT) will be calculated to assess the effectiveness of the drugs, while the number needed to get severe side effects will be calculated as NNF. During analysis subjects will be adjusted according to exposure to neurotoxic drugs. Analysis will also be done using the intention to treat analysis, where all randomised subjects will be included in the analysis to reduce bias.

The number treated analysis will also be done looking only at those subjects who managed to reach the maximum dose of the drugs. This however is subject to selection bias as subjects who developed side effects and those who were lost to follow up will be excluded. The effect of the use of other pain medication in together with the intervention being tested will also be analysed.

The results will be adjusted for ART during analysis, as all patients including those already on ART will be included in the study.

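### The primary outcome is described in three ways; taken as the within-period change, it subtracts a noisy start score, which is never more precise than adjusting for that score

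*Protocol*

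**What the plan says.** The protocol describes the primary outcome in three places.

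- Study Summary, primary objective: "A measurement of the difference in pain intensity at the beginning and end of each 6 week treatment period". This is a change score for each period.
- Primary outcome measures: "Self reported pain intensity measurement is the primary outcome measure". No time point is given, and it is not said whether a level or a change is meant.
- Data collection, management and analysis (the section after Quality control): "The primary outcome (pain relief between baseline and end of the study) will be compared for the" two ANOVA comparisons that follow. Adjustment is planned for neurotoxic drug exposure and for ART. Baseline pain is not named as a covariate.

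The Cross over design section says that "the baseline pain intensity will be measured at the start of each treatment intervention", so both period-start scores will exist. The same section gives the patient acting as their own control as a reason for the design.

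Sample size calculations gives "effect is difference of 2 on a 0-10 scale; variance is 2SD", with 90% power and alpha 0.05. It does not say whether the SD belongs to a single score, a change, or a within-patient difference. It then states: "For a cross-over design 46 participants will be required".

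**The concern.** The analysis section conflicts with the Study Summary. By week 15 every patient has had both treatments, so a change from enrolment to week 15 is not a treatment contrast. Reading the end of the study as week 6, because the Side effects section speaks of a 6-week study, would leave only the first period. Neither reading matches a change measured in each period.

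The Study Summary version also has a cost of its own. Its contrast is (end minus start on amitriptyline) minus (end minus start on placebo). A cross-over already removes stable differences between patients, so subtracting the two start scores brings in two more noisy readings. In addition, the start score of period 2 is taken after period 1 treatment, so any residual drug effect at that visit enters the change.

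At stake are the precision of the main estimate, above all within each ARV stratum, and the freedom to choose between definitions that give different estimates and standard errors from the same patients.

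**Working it through.** **Inputs.** From the protocol: a 2-point difference, an SD of 2 (read here as the SD of a single score), 90% power, alpha 0.05 (taken as two-sided), 46 participants required, 62 enrolled per ARV stratum, and about 10% loss. That leaves 62 × 0.9 = 55.8, about 56 completers per stratum. Correlations are not given and are assumed: w between start and end of the same period, b between any two scores from different periods.

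**The plan's own figure.** The two-group t formula with difference 2 and SD 2 gives 23 per group, so 2 × 23 = 46. A cross-over calculation on change scores, with four uncorrelated scores of SD 2, has contrast SD √(4 × 2²) = 4 and needs 45. The figure of 46 therefore does not reveal which quantity the SD describes.

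**Variances per patient**, with score SD s and c = (w − b)/(1 − b), the correlation between the start difference and the end difference:

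- end-of-period pain, unadjusted: 2s²(1 − b)
- within-period change: 4s²(1 − w) = 4s²(1 − b)(1 − c)
- end-of-period pain adjusted for the start difference: 2s²(1 − b)(1 − c²)

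Change over adjusted is 2(1 − c)/(1 − c²) = 2/(1 + c). Since c cannot exceed 1, the ratio is never below 1. The change score fixes the slope on the start difference at 1, whereas least squares picks the slope that minimises the variance. Estimating the slope costs one degree of freedom, ignored here. Change over unadjusted is 2(1 − c), which exceeds 1 only when c < 0.5.

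**Values at s = 2:**

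| w | b | c | unadjusted | change | adjusted | change/adjusted | change/unadjusted |
|---|---|---|---|---|---|---|---|
| 0.5 | 0.5 | 0 | 4.00 | 8.00 | 4.00 | 2.00 | 2.00 |
| 0.7 | 0.5 | 0.4 | 4.00 | 4.80 | 3.36 | 1.43 | 1.20 |
| 0.8 | 0.5 | 0.6 | 4.00 | 3.20 | 2.56 | 1.25 | 0.80 |
| 0.8 | 0.3 | 0.71 | 5.60 | 3.20 | 2.74 | 1.17 | 0.57 |
| 0.5 | 0.6 | −0.25 | 3.20 | 8.00 | 3.00 | 2.67 | 2.50 |

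The last two rows are the extremes of change/adjusted over b = 0.3 to 0.6 and w = 0.5 to 0.8. A simulation at w = b = 0.5 gave 3.99 (unadjusted) and 7.98 (change).

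**One stratum, 56 completers, normal approximation.** Detectable difference at 90% power is (1.960 + 1.282) × SE.

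- w = b = 0.5: SE is √(4/56) = 0.267 adjusted and √(8/56) = 0.378 for the change. Detectable differences are 0.87 and 1.23; power for a 1-point effect is 96% and 75%.
- w = 0.7, b = 0.5: SE is √(3.36/56) = 0.245 and √(4.8/56) = 0.293. Detectable differences are 0.79 and 0.95.

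**Planned effect.** With 46 patients, a 2-point effect and all correlations zero, the change contrast has SD 4 and power is about 91%. With all correlations 0.5 it is 99.7%.

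**Carry-over.** Suppose a residual effect r lowers the day-63 score in the amitriptyline-first sequence and is gone by week 15. That sequence's placebo change then looks worse by r. Averaged over two equal sequences, the bias is r/2 in favour of amitriptyline. Adjustment multiplies the start difference by c instead of 1, so the bias becomes about c × r/2: 0.2r at c = 0.4 and 0.3r at c = 0.6. Unadjusted end-of-period pain carries none of it in this scenario.

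**The case against.** A reader might infer that the Study Summary and the section on primary outcome measures contradict each other, one giving a change and the other a level. The text does not support that. The second names the variable and no time point, and the first can be read as its specification. The firm conflict is between the Study Summary and the analysis section.

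A reader might also infer that the change score doubles the variance and so undermines the sample size. Doubling needs w = b, and the protocol gives no correlations. Against unadjusted end-of-period pain the change score is the better choice once c exceeds 0.5, as at w = 0.8, b = 0.5. With single-score SD 2, 46 patients keep about 91% power for 2 points even with zero correlations. Power would fall materially, to 65% with 46, only if the end-of-period contrast itself had SD 4 and its variance doubled to SD 5.66. The protocol does not say so.

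A within-period change is a valid measure, unbiased without carry-over, and the handling of period baselines is often left to an analysis plan. That is fair as far as it goes. But the protocol itself makes the change the primary measure and names an ANOVA without baseline pain, and the ratio 2/(1 + c) favours adjustment whatever the correlations.

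On carry-over, the planned washout is 21 days (day 42 to day 63) against the protocol's own figure of 18.75 days, and the size of r is unknown. The proposed analysis shares part of the bias. This is a secondary argument, and no actual bias is shown.

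**Conclusion.** The point holds in limited form. The primary outcome needs one definition with a time point, and the SD of 2 needs a stated meaning. If the within-period change is kept as the primary measure, precision is given away: its variance is 2.0, 1.43 or 1.25 times that of the baseline-adjusted analysis in the three main cases, and 1.17 to 2.67 times over the assumed grid. The direction does not depend on the assumptions; the size does. It rests on equal score SDs, a single between-period correlation and assumed values of w and b.

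The consequence is wider intervals and lower power for effects smaller than planned, mainly within each ARV stratum. Loss of power for the 2-point effect is not shown. It should be corrected, but it does not put the planned primary comparison at risk.

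**What to change.** In the Study Summary, Primary outcome measures, and Data collection, management and analysis, define the primary endpoint once: pain intensity on the 0-10 scale at the end of each 6-week period. Compare amitriptyline with placebo within patient, with period in the model and the within-patient difference of the two period-start scores as a covariate. Report the within-period change descriptively. In Sample size calculations, state which quantity the SD of 2 describes.

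The cost is wording only. Both period-start scores are already to be collected, so no extra data are needed. The downsides are that the within-period change is no longer the headline result, and that some carry-over bias would remain if a residual effect were present at day 63.

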## **Background:**

### ***Neuropathic pain in HIV***

Moderate to severe neuropathic pain will be experienced by a considerable proportion of people with HIV, adversely affecting their activities of daily living, mood and sleep, fatigue and may have an impact on physical or social functioning. It can be debilitating to the point of severe mobility restriction. Unlike nociceptive pain neuropathic pain has no protective role but the exact mechanisms involved in the generation of various neuropathic pains remain elusive. Neuropathic pains in HIV represent heterogeneous clinical conditions which cannot be explained by a single mechanism. Clinical conditions which relate to HIV infection include inflammatory demyelinating polyneuropathy, mononeuritis multiplex, progressive radiculopathy. Aetiologies vary and are thought to arise from: ARV therapy especially with dideoxynucleosides (stavudine/D4T, a first line treatment in South Africa); damage from the virus itself; vitamin B12 deficiency; those caused by opportunistic infections, for example a post-herpetic neuralgia, treatment with other drugs such as anti TB drugs.

This trial will look at the effectiveness of treatment for the most common form of HIV related neuropathy, distal sensory neuropathy (DSN). Studies have estimated that distal sensory neuropathy (DSN) is present in up to 40%-50% of people with HIV on antiretroviral therapy (ARV) and 90-100% of those with DSN have pain(1). This has not changed with improvements in ARV therapy. Increased survival with ARV therapy has led to an increase in the prevalence of DSN. Risk factors for the development of DSN include advancing age, higher peak plasma viral load levels, exposure to didanosine drugs and protease inhibitors. (2) There are two sub-types of DSN: the type solely associated with HIV infection and the type associated with ARV therapy, sometimes referred to as acute toxic neuropathy (2). Work at the palliative care unit at Wits has demonstrated effective pain and symptom relief, using a validated tool (Wits ethics number M060366) in patients with HIV. However a subset of patients has not responded to current pain treatment protocols. It is postulated that these patients with 'difficult' pain are those with neuropathic pains. Effective pain management in HIV may improve adherence to ARV therapy, especially when the pain is caused by the ARV therapy itself.

### ***What is known about treating HIV related DSN***

Clinical trials have shown that treatments effective in other disease states cannot be transferred to HIV DSN(2). Thus the effective use of drugs such as amitriptyline or other tricyclics, carbamazepine, lamotrigine, gabapentin, or other anti-convulsants; opioids or indeed drug combinations in other disease states do not necessarily mean effectiveness in HIV DSN. The results of negative trials in HIV DSN include assessment of acupuncture, mexiletine, peptide T. Other RCT results are listed below.

Results of randomised controlled trials carried out in this area:

| Drug          | Comment                     | effectiveness             |
|---------------|-----------------------------|---------------------------|
| Lidocaine     | Small trial                 | none                      |
| Gabapentin    | Small trial (3)             | Could be effective        |
| Amitriptyline | 2 trials, see details below | Not effective             |
| lamotrigine   | Conflicting evidence(4;5)   | One trial yes, another no |

Also drugs which may have interaction with ARVs have been excluded for consideration, for example sodium valproate. New treatments, including an open labelled study which suggests that capsaicin is effective, are on the horizon but treatment costs and future drug availability and timelines for evidence are uncertain. There are no non-drug interventions which have been shown to be effective for HIV –DSN.

Current guidelines internationally recommend either gabapentin, amitriptyline or lamotrigine. Nationally amitriptyline is recommended. None of these are based on high grade evidence. There have been two RCTs evaluating amitriptyline for pain due to HIV related distal sensory neuropathy(6;7). One by Shlay and co-workers in 1998 compared amitriptyline to acupuncture and matching placebo. The second trial by Keiburtz et. al compared amitriptyline to mexiletine and matching placebo. Both showed no effect for amitriptyline. However we are proposing that it is important to conduct this trial for reasons which are elucidated below;

- The study populations in the two trials are different to the ones we propose.
  - White (70-82%) male (96%) with mild to severe pain

- In the light of newer work on the role of response variation with genotype to the development of DSN, trials are warranted in a South African population (8;9) (10)
- Both trials included participants with all grades of pain, and in both trials the mean for baseline pain were mild or moderate. The European Medicines Agency recommend that trials are conducted in people with moderated to severe pain, since in a mild pain population a high response to placebo can be expected(11)
- Both trials had limitations in terms of enrolment numbers not reaching calculated samples sizes or original trial design
- One trial found a trend for improvement of pain in the amitriptyline group

Finally amitriptyline is widely used for this condition in South Africa. It is the drug of choice for many treatment protocols throughout the country. Personal communication with Aspen Pharmaceutical indicates that the bulk of their brand (trepiline) is used for DSN. In addition it is recommended in the South African palliative care national guidelines, by the SA HIV Clinicians society and the Foundation for Professional Development for HIV related DSN. Thus it is important to support or refute existing evidence in a population that is clinically relevant to South Africa.

